### Community sensitization

Community sensitization will be conducted to inform community leaders and community members about the study objectives, study rationale and to request their co-operation during study implementation. All attendees of the community sensitization meetings will be encouraged to ask questions from the study investigators to enable the community to understand the study objectives and the risks and benefits of study participation.

### Baseline surveys and distribution of ITNs

Upon obtaining written informed consent from the head of household or adult resident, field workers that have been trained on the study protocol and procedures will conduct the baseline questionnaire as outlined in Lorenz et al. [41] and will distribute the nets required for each household with one net distributed per sleeping space. Non-study nets found in the households will be withdrawn from households to ensure only study ITNs will be present and used in the households. In Tanzania, the withdrawn nets will be stored in bags labelled with the name of the household head and the study village to be returned to their respective households after the study, while the withdrawn nets will be discarded in Côte d’Ivoire and India following specific country procedure. Handling of withdrawn nets is different between countries because of differences in ethical considerations and regulations between countries.

The questionnaire forms will be written in local languages; Kiswahili for Tanzania, French for Côte d’Ivoire and Telugu for India, and will be pre-loaded in Open Data Kit (ODK) Collect software installed on a hand-held Samsung Tab A tablet computer. Data collected during the baseline surveys will be used as the household roster (names, ages, sex, education, occupation and the relationship to the household head), household wealth indicators [42], house characteristics, number of sleeping areas, ownership of mosquito nets, use of mosquito nets, net attitude indicators [43] and household coordinates in the global positioning system (GPS).

## Randomization to study arms

### ITNs distribution

After the baseline survey questionnaire has been completed, on the same day one out of the four products of ITNs will be assigned to the household based on block randomization using a lottery method. All net types are packaged in identical cloth bags. Each field interviewer is given a large bag containing all four products that they select at random and once the net is selected, additional nets of the same product (starting with the same digit code) will be provided to cover all sleeping areas in the household.

### Generating master lists for follow-up: attrition, fabric integrity and bio-efficacy

The unique identifiers (UID) consist of six numbers generated by the study statistician—the first number identifies the country, the second identifies the treatment arm and the remaining four numbers identify nets distributed per arm. At baseline, the UID of each ITN given to the household will be recorded in the baseline questionnaire and in the ITNs master list with each unique net identification code linked to the household identifying codes and GPS coordinates. Two lists will be generated using a random number generator from the household masterlist: (1) attrition and fabric integrity monitoring masterlist (A-list) and (2) destructive sampling for bio-efficacy and chemical retention monitoring masterlist (B-list). These are separate because bio-efficacy and chemical retention monitoring will require ITNs to be removed from the cohort and replaced with new nets. For attrition and fabric integrity monitoring, the same ITNs will be followed up to the end of the study period unless the household is lost to follow-up or withdraws consent.

### Follow-up surveys

Study ITNs per household visited during attrition monitoring at 6, 12, 24 and 36 months will be inspected for fabric integrity. All study ITNs listed in the master list provided will be inspected while non-study nets found in the household will only be recorded. In the households selected for bio-efficacy testing, the first ITN listed will be withdrawn, and if that ITN is not present in the household, the second ITN on the list provided will be sampled. If no study ITNs are present in the household, another household with the same net product will be visited as a replacement.

#### Adverse effects and ITN usage

One month after distribution, 250 households for each ITNs product will be selected randomly from the household master list for the assessment of ITN usage and adverse events. The head of the selected households will be interviewed on perceived adverse effects from all members using the adverse effect questionnaire adapted from the WHO guideline [8].

#### Monitoring attrition

Attrition (the proportion of ITNs no longer found in their respective households) will be assessed at 6, 12, 24, and at 36 months after distribution. After 6 months, 2712 individual households (678 per product per location) will be selected randomly from the A-list prepared for each country separately. The same households will be followed up longitudinally at 12, 24 and 36 months. The presence or absence of all the ITNs that were distributed will be recorded and if absent, the reasons for absence in the household will be provided by the head of the household. ITNs missing due to wear and tear will be considered as lost due to attrition, and those missing because they were stolen, sold or given away to others, will be considered as lost to follow-up.

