### Sample size

#### The sample size for the ITN surveys

The sample size was calculated based on the primary outcome measure of net attrition together with additional nets for the bio-efficacy components. Assuming an average of 2.7 nets per household and a coefficient of variation of 0.25, the formula on page 110 of Hayes and Moulton [59] gives a sample size of 678 households per arm to detect the difference in attrition between two products assuming 3-year attrition rates of 47.5% and 52.5% with 80% power. An additional 260 households for bio-efficacy, chemical analysis and IACT have been added to 678 making a total number of 938 households. Since the median lifespan of ITNs products from durability studies in Tanzania is less than 3 years [29, 60, 61], a 41% loss to follow-up of households is assumed making addition of 657 households to the 938 households. The final total number of households that will be recruited at baseline per product per country is 1595. With an average of 2.7 nets per household [62], the total number of ITNs required per product per country will be 4521 including 5% for error due to poor quality or nets with open seam prior to distribution, Table 5.

**Table 5 Tab5:** Description of the numbers of ITNs distributed in the study area

Households for longitudinal attrition and fabric integrity monitoring	678
Households for I-ACT, cone bioassay and chemical testing	260
Unadjusted total households per product per country	938
Loss to follow up households	657
Adjusted total households per product per country	1595
The average number of ITNs per household per product	2.7
Total ITNs per product	4305
5% error and nets for replacement	215
Total ITNS required for each product per country	4521

The same net used in the IACT will be used for cone bioassay and chemical testing

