### Data analysis

All data analyses will be conducted using STATA software (Stata Corp LLC, College Station TX, USA). The durability outcomes; attrition, fabric integrity, bio-efficacy and insecticide content will be estimated (Table 4). These outcomes will be estimated for each net product by survey period and country. A pooled estimate from three countries will also be presented, if appropriate.

The non-inferiority of Veeralin® and Tsara® Boost nets to Olyset® Plus will be carried out using logistic regression for the binary outcome of mosquito mortality with ITN product, compartment, volunteer and day as covariates. A random effect for chamber-night will be included. The 95% confidence interval for the estimated odds ratio for the effect of Tsara Boost® and Veeralin® compared to Olyset® Plus will be presented. Non-inferiority is shown if the confidence interval excludes an unacceptably worse performance. The bound of the margin of non-inferiority for mortality will be set at 0.7. If the lower bound of the confidence interval for the effect of the candidate net compared to Olyset® Plus is greater than 0.7, then we will conclude that the net product is non-inferior [36].

The utility of washed nets as a proxy for field nets will be assessed on the mortality and blood-feeding inhibition endpoints using logistic regression. The estimated odds ratios for the effect of washed nets compared to the negative control, and field-aged nets compared to the negative control will be presented. The ratio of these odds ratios will be estimated along with the 95% confidence interval using interaction terms in the logistic regression model.

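### The attrition cohort starts at 678 households per product, the number needed after loss, so on the plan's own 41% loss per-country power at 36 months is about 57–61%, not 80%

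*Protocol article*

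**What the plan says.** In the Protocol article, the section on the sample size for the ITN surveys makes attrition the sizing outcome: "The sample size was calculated based on the primary outcome measure of net attrition together with additional nets for the bio-efficacy components". The inputs are "Assuming an average of 2.7 nets per household and a coefficient of variation of 0.25" and "assuming 3-year attrition rates of 47.5% and 52.5% with 80% power". The cited cluster-trial formula "gives a sample size of 678 households per arm to detect the difference in attrition between two products". The plan then adds 260 households for bio-efficacy, chemical analysis and chamber testing, which gives 938. For loss, "a 41% loss to follow-up of households is assumed making addition of 657 households to the 938 households", which brings recruitment to 1595 per product per country. Table 5 repeats these steps and lists 678 as the households for longitudinal attrition and fabric monitoring.

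The section on monitoring attrition then sets the cohort: "After 6 months, 2712 individual households (678 per product per location) will be selected randomly from the A-list prepared for each country separately". It continues: "The same households will be followed up longitudinally at 12, 24 and 36 months".

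The section on generating master lists expects some households in this cohort to be lost or to withdraw. The only replacement rule for households, under Follow-up surveys, concerns those selected for bio-efficacy sampling.

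**The concern.** The number 678 has two roles that cannot both hold once any household is lost. In the sample size section it is the number of households that must contribute to the 3-year comparison, before any allowance for loss. In the follow-up section it is the starting size of a closed cohort observed for a further 30 months. The allowance is made at recruitment, but nothing stated brings the additional households into attrition measurement after the month-6 draw.

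At stake is the 80% power claimed for the outcome that sized the trial, at the time point and on the per-country basis for which it was calculated. A reader of a null pairwise comparison in one country would take it as coming from a well-powered test when it may not have been.

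A second, smaller difficulty lies in the reason given for 41%. It rests on median net lifespans under three years. A worn-out net is the attrition event, not a household lost to follow-up, so the reason does not support the figure.

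**Working it through.** **Inputs.** From the sample size section: p0 = 0.475, p1 = 0.525, m = 2.7 nets per household, k = 0.25, power 80%, household loss 41%. The significance level is not stated for this calculation. I assume two-sided 0.05, because it reproduces 678 and one-sided 0.05 does not (534–535). The nearest support in the text is "The 95% confidence interval for the estimated odds ratio", which belongs to the non-inferiority analysis.

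**Step 1: reproduce the plan's figure.** Unmatched cluster formula for two proportions, household as cluster:

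c = (z_α/2 + z_β)² × V / (p1 − p0)², with V = [p0(1−p0) + p1(1−p1)]/m + k²(p0² + p1²).

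- V = 0.49875/2.7 + 0.0625 × 0.50125 = 0.18472 + 0.03133 = 0.21605.
- c = (1.960 + 0.842)² × 0.21605 / 0.0025 = 678.3, or 679.3 with the formula's added 1.

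So 678 reproduces, and it contains no allowance for loss.

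**Step 2: reproduce the allowance.** 657/1595 = 41.2%, and 938/0.59 = 1590, close to the stated 1595. The 41% is thus a proportion of those recruited. Applied to the two parts separately:

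- Attrition list: 678/0.59 ≈ 1,150.
- Bio-efficacy list: 260/0.59 ≈ 441. The 260 is the sum of the planned net samples at 6, 12, 18, 24, 30 and 36 months: 30 + 60 + 30 + 60 + 30 + 50.

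These add to 1,591. Recruitment is therefore large enough for an attrition cohort of about 1,150 per product, but only 678 are drawn.

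**Step 3: power for the cohort actually followed.** Inverting the same formula, power = Φ(√(c × 0.0025/V) − 1.96), with c replaced by c − 1 if the added 1 is kept.

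- Full 41% loss after selection: 678 × 0.59 = 400. √(400 × 0.0025/0.21605) = 2.151, and Φ(0.191) = 0.576 (0.575 using 399).
- The 41% accrues at a constant rate over 36 months and only households still present at month 6 are drawn: retention from month 6 to 36 is 0.59^(30/36) = 0.644, so 437 households remain and power is 0.61.

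Other losses after selection (my assumption, to show the range):

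| Loss after selection | Households at month 36 | Power |
|---|---|---|
| 5% | 644 | 78% |
| 10% | 610 | 76% |
| 20% | 542 | 71% |
| 30% | 475 | 65% |

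**Step 4: detectable difference at 400 households, 80% power.** Keeping the two rates centred on 50%, at a difference of 0.065 V = 0.2158. Then √(2.802² × 0.2158/399) = 0.065, so about 6.5 points, against 5.0 planned.

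**Step 5: two alternative readings.**

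- If the 41% describes nets and not households, all 678 households stay with m = 2.7 × 0.59 = 1.59, and power is about 60%.
- If the three countries are pooled, 3 × 400 = 1,200 households per arm give about 96%.

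**The case against.** Several points on the other side are fair.

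- **The size depends on an input that is itself doubtful.** If net wear-out is the only ground for 41%, true household loss is unknown and could be much smaller. Worn-out nets stay in the attrition denominator and cost no power. This stands: 57% follows from the plan's own assumption and is not a forecast, so the result should be given as a range.
- **The draw comes after month 6**, so a larger list can absorb early losses. That is possible, although the text does not say that departed households are screened out. It moves the figure to about 61%.
- **The reserve is not idle.** A reader might infer that all 657 extra households serve no purpose. The documents do not support that: about 181 of them (441 − 260) correspond to the bio-efficacy list, where replacement is explicit. What can be said is that no use of the rest for attrition after month 6 is stated.
- **The outcome rule is sound.** A reader might also infer that the plan counts worn-out nets as lost to follow-up. It does not. The section on monitoring attrition counts wear and tear as attrition, and treats only stolen, sold or given-away nets as lost. Only the rationale for the 41% is muddled.
- **The objective is estimation, and pooling is foreseen.** The secondary objectives ask for attrition rates by product and location. With the same m and k, the 95% half-width around 50% is 1.96 × √(0.1082/400) = 3.2 points at 400 households and 2.5 at 678, which is a modest loss. Pooled power would remain high. But the sample size is set and justified per country as a two-product comparison, and the Data analysis section makes pooling conditional.

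That an article condenses a longer protocol does not remove the point. Both sections state 678, in roles that conflict.

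**Conclusion.** The point holds for the per-country pairwise comparison at 36 months. The stated 80% requires 678 households to remain, whereas the cohort starts at 678. On the plan's own 41%, power is about 57–61%. At 10–30% loss after selection it is 76–65%, and any loss at all takes it below 80%.

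The result rests on two-sided 0.05, the plan's m and k, and no use of reserve households beyond what is stated. It should not be read as saying that power is 57% whatever happens, or that the trial cannot compare attrition: the pooled comparison would still have about 96% power if pooling is judged suitable. The fault is that the loss allowance is not carried from recruitment into the closed cohort, together with a reason for the 41% that describes the outcome and not loss to follow-up.

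**What to change.** 1. **Restate the power (minimum fix).** In the sample size section, give per-country power or the detectable difference for a cohort that starts at 678, as a range over loss after selection. For example: 76%, 71% and 65% at 10%, 20% and 30%, and about 57–61% (about 6.5 points detectable at 400 households) under the 41% assumption. State the significance level. This costs one corrected paragraph.
2. **Or use the reserve, where visits allow.** State how already recruited reserve households enter attrition measurement, and record net presence in them at the remaining surveys, aiming for about 1,150 per product per country (678/0.59). No new enrolment is needed, since these households hold coded nets linked to baseline records. The visits are the cost: 1,150 − 678 = 472 more households per product, about 70% more, or 472 × 4 × 3 = 5,664 per round over all products and countries, with hole counts on top if fabric integrity is included. According to Current study status, follow-up is under way and the month-6 draw may have passed, so this may be possible only for later rounds.
3. **Justify the 41% as household loss** (moving away, refusal, not found), or replace it with a figure that can be supported. Net lifespan should not be the reason. The definition of attrition needs no change.

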#### Monitoring fabric integrity

Each ITN found during the attrition monitoring will be draped over a collapsible net frame [41] and the number of holes of four different sizes categories [8] will be counted by their locations on the net, recorded in a hole tally sheet and entered in the follow-up questionnaire. The locations of the net are obtained by dividing the side panels into four equal zones from top to the bottom and a roof as a fifth location of the net [41]. The four-size categories of the holes are 0.5–2 cm, 2–10 cm, 10–25 cm, and above 25 cm for sizes 1, 2, 3 and 4, respectively approximated using a thumb, fist, head and larger than a head [44]. The overall physical condition of the net will be obtained by weighting the number of holes of each size by 1, 23, 196 and 576 for the four-size categories of holes (based on the average assumed surface area for each size category) to obtain a proportionate hole index (pHI) following WHO guidelines [8]. The pHI value obtained will be used to classify the net as serviceable if the pHI value is less or equal to 642 and too torn if the pHI value obtained is greater than 642 [44].

Additionally, three new nets per product from the same production batch used in this study will be assessed for the Resistance to Damage (RD) score [31] at CITEVE (Centro Tecnológico das Indústrias Têxtil e do Vestuário de Portugal). The RD score is a quantitative metric based on four standardized textile tests taking into account different mechanisms of damage to ITNs including both human factors for damaging the net and laboratory testing data [45, 46]. The average value of standardized laboratory textile test data for snag strength, bursting strength, abrasion and hole enlargement [47] is divided by four so that each laboratory parameter contribute equally to the overall RD value which is expressed in percentage with a value ranging between 0 and 100 [31].

### Monitoring bio-efficacy

#### Mosquito species

Pyrethroid susceptible and pyrethroid-resistant strains will be used for bio-efficacy testing in each country. Mosquitoes are maintained following MR4 guidance [48] by feeding larvae on Tetramin fish food and adults on blood meal between 3 and 6 days after emergence and 10% glucose solution ad libitum. All mosquitoes are maintained inside cages in different rooms to prevent cross-contamination. Temperature and humidity within insectaries are between 27 °C ± 5 °C and 70% ± 20% relative humidity, respectively.

In Tanzania, metabolic pyrethroid-resistant *Anopheles arabiensis* Kingani strain and a full pyrethroid susceptible *Anopheles gambiae *sensu stricto (s.s.) Ifakara strain will be used. In Côte d’Ivoire, metabolically resistant *An. gambiae* s.s. Tiassalé strain and a fully pyrethroid susceptible *An. gambiae s.s.* Kisumu strain will be used. In India, a pyrethroid-resistant *Anopheles culicifacies* strain and a fully pyrethroid susceptible *Anopheles stephensi* strain will be used. The bio-efficacy outcomes will be reported separately for each strain in each country. The susceptibility status of the susceptible and resistant strains will be confirmed at least twice per year in each country following standard procedures [49, 50] during the study period. If the susceptibility status changes during the study, a new colony will be established by either selecting resistant mosquitoes from a mixed colony or re-establishing a new colony from the original source.

#### Mosquito net sampling and preparation

Cone bioassays will be conducted at baseline using 30 nets per product from B-list to ensure nets are of sufficient quality before distribution. At baseline, five net pieces (25 cm × 25 cm) will be cut from position 1 to position 5 of the net as per WHO guidelines [8] and all net pieces will be tested in cone bioassay [38]. For each sampled net from the field, four net pieces (25 cm × 25 cm) will be cut from position 2 to position 5 of the net and tested in cone bioassay. A piece from position 1 (the bottom of the net) will not be cut, as it may be exposed to excessive abrasion due to tucking under the bed [38].

Bio-efficacy testing will be conducted on a total of 30 nets (one from each of 30 households) sampled at random from the B-list for each product at 6, 12, 18, 24, and 30 months post-distribution survey. Only at 36 months, 50 nets per product will be sampled for bio-efficacy and chemical testing estimates. However, 60 (30 selected for bio-efficacy testing and a further 30) nets per product will be sampled at 12 and 24 months for additional testing in the IACT [51]. If the listed ITN is not present, another net (of the same product) within the same household will be selected. After a net is withdrawn for bio-efficacy testing, the household will not be eligible for a next round of bio-efficacy sample collection from the B-master list. The withdrawn net samples will be replaced. The head of the household will be offered any of the ITN products in the trial and allowed to select their replacement based on preference, and this choice will be recorded.

#### WHO cone test procedure

The WHO cone bioassays will be conducted separately at the (1) Vector Control Product Testing Unit (VCPTU) in Bagamoyo, Tanzania, (2) Swiss Centre for Scientific Research (CSRS) in Tiassalé district, Côte d’Ivoire, and 3) ICMR-National Institute of Malaria Research (NIMR) field unit in Bengaluru, Karnataka state, India. Four cones will be attached to each net piece and 5 mosquitoes exposed per cone, 100 mosquitoes per strain at baseline and 80 mosquitoes per strain at each post-distribution survey to each ITN [8]. Non-blood-fed, 2–5 days old, female mosquitoes each of the susceptible and resistant strains for the PBO nets and susceptible strain for the pyrethroid only net will be exposed to the ITN for 3 min [8]. After the exposure, mosquitoes will be removed and kept in holding cups provided with 10% glucose or sucrose solution. Mosquito knockdown will be recorded after 60 min (KD_60_) and mortality after 24-h (M_24_). ITNs that do not meet WHO bio-efficacy thresholds of KD_60_ ≥ 95% or M_24_ ≥ 80% with the susceptible mosquito strains will be tested in the WHO tunnel test [8].

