**Methods:**

A prospective household randomized controlled trial will be conducted simultaneously in Tanzania, India and Côte d’Ivoire to estimate the field durability of three pyrethroid-PBO ITNs (Veeralin®, Tsara® Boost, and Olyset® Plus) compared to a pyrethroid LLIN: MAGNet®. Durability monitoring will be conducted up to 36 months post-distribution and median survival in months will be calculated. The proportion of ITNs: (1) lost (attrition), (2) physical integrity, (3) resistance to damage score, (4) meeting WHO bio-efficacy (≥ 95% knockdown after 1 h or ≥ 80% mortality after 24 h for WHO cone bioassay, or ≥ 90% blood-feeding inhibition or ≥ 80% mortality after 24 h for WHO Tunnel tests) criteria against laboratory-reared resistant and susceptible mosquitoes, and insecticidal persistence over time will be estimated. The non-inferiority of Veeralin® and Tsara® Boost to the first-in-class, Olyset® Plus will additionally be assessed for mortality, and the equivalence of 20 times washed ITNs compared to field aged ITNs will be assessed for mortality and blood-feeding inhibition endpoints in the Ifakara Ambient Chamber Test, Tanzania.

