Bed nets that retain their bio-efficacy thresholds (the proportion of mosquitoes (≥ 95%) knocked down after one hour or (≥ 80%) mortality after 24 hours for cone bioassay, or if cone bio-efficacy thresholds are unmet, the proportion of mosquitoes (≥ 90%) blood-feeding inhibition or (≥ 80%) mortality after 24 h for tunnel tests) for at least 20 World Health Organization (WHO) standard washes under laboratory conditions and three years of recommended use under operational conditions are qualified as LLINs [8, 14]. However, it is not known if the 20 times WHO laboratory washed ITNs correspond to the field-used ITNs in inducing mosquito mortality. Also, although the WHO has prequalified several pyrethroid-PBO ITNs, there is currently limited data available on their physical and insecticidal durability under operational conditions in different geographical regions [8]. Understanding the durability of pyrethroid-PBO ITNs under operational conditions is important to guide procurement decisions and for devising replacement policies [21].

The physical integrity of a LLIN under operational conditions is one of the key determinants of net retention in the household, and more than 75% of discarded LLINs have damage and are perceived as failing to protect the user [22]. Factors associated with the loss of the physical integrity of LLINs include the environment in which the net is used [23–25], the users’ net care behaviour and attitude towards the LLIN [26], the type of net material [27–30], snag strength, bursting strength, abrasion resistance and resistance to hole enlargement [31], the number and age of people sleeping under the net [32, 33], and the geographical location in which the net is used [34]. Therefore, it is recommended to conduct ITN durability studies in multiple geographical locations [8]. The current study aims to measure the insecticidal and physical durability of three PBO ITNs alongside a pyrethroid only net over three years of household use in three different regions.

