#### WHO tunnel test

Each site will perform tunnel tests independently on each ITN that did not meet WHO efficacy criteria (i.e., ≥ 95% KD_60_ or ≥ 80% M_24_) in the cone test against the susceptible strains of mosquitoes, only one out of four net pieces will be selected for the tunnel test. This is the piece that gave mortality closest to the average mortality in the cone test of the four pieces (i.e., average for that net). The selected piece will be fixed in the tunnel for testing. One tunnel with untreated netting will be used as a negative control. Fifty non-blood fed female susceptible *Anopheles* mosquitoes aged 5–8 days sugar starved for 6–8 h will be released in a tunnel (square section 25 cm × 25 cm) made of glass, 60 cm in length [8]. For pyrethroid only nets, susceptible mosquitoes will be used, while for PBO nets, both susceptible and resistant strains will be used.

At one-third of the length, the netting sample is fixed, with the surface of netting available to mosquitoes of 400 cm^2^ (20 cm × 20 cm) with nine holes each 1 cm in diameter: one hole is located at the centre of the square; the other eight are equidistant and located at 5 cm from the border. In the shorter section of the tunnel, a small rabbit, which will be restrained and unable to move but available to mosquitoes, will be placed as bait. To minimize discomfort to the rabbits, all applicable experimental animal welfare procedures will be adhered to following specific country regulations. In the cage at the end of the longer section of the tunnel, 50 female mosquitoes [52] will be introduced at 18:00. The following morning from 09:00, the mosquitoes will be removed using a mouth aspirator and counted separately from each section of the tunnel and mortality and blood-feeding rates will be recorded. During the test, ambient conditions will be maintained at 27 °C ± 5 °C and 60–100% relative humidity. Acceptable feeding success and mortality in controls will be ≥ 50% and ≤ 10%, respectively.

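### The tunnel test is triggered only by susceptible-strain cone failure, so a combined cone-or-tunnel pass rate against the resistant strain depends on how the net did against the susceptible strain

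*Protocol article*

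**What the plan says.** All points are in the protocol article.

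- **Cone exposure (WHO cone test procedure).** Mosquitoes are "each of the susceptible and resistant strains for the PBO nets and susceptible strain for the pyrethroid only net". Every sampled PBO net thus has a cone result for each strain; MAGNet has one for the susceptible strain only.
- **Trigger (same section).** Nets that miss the knockdown and mortality thresholds "with the susceptible mosquito strains will be tested in the WHO tunnel test".
- **Trigger repeated (WHO tunnel test).** The tunnel is for nets that did not meet the criteria "in the cone test against the susceptible strains of mosquitoes, only one out of four net pieces will be selected for the tunnel test".
- **Strains in the tunnel (WHO tunnel test).** "For pyrethroid only nets, susceptible mosquitoes will be used, while for PBO nets, both susceptible and resistant strains will be used".
- **Outcome (abstract, Methods).** The proportion of nets meeting the WHO cone or tunnel "criteria against laboratory-reared resistant and susceptible mosquitoes, and insecticidal persistence over time will be estimated".
- **General role of the tunnel (Background).** It applies "or if cone bio-efficacy thresholds are unmet", with no strain named.
- **Reporting (Mosquito species).** "The bio-efficacy outcomes will be reported separately for each strain in each country".
- **Table 4.** Biological efficacy is defined by the effect on susceptible anophelines; the resistant strain is not mentioned.

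**The concern.** For the susceptible strain the sequence is coherent: fail the cone, go to the tunnel, pass if either test is passed. For the resistant strain the second chance is tied to a different test. A PBO net that still kills susceptible mosquitoes but fails the cone against resistant ones is not sent to the tunnel. A net that fails against both strains is sent, and can be credited with a resistant-strain pass there.

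The group left out is a plausible one. The Discussion cites large losses of PBO from Olyset Plus in field use, and a net that has lost synergist but kept pyrethroid could well pass the susceptible cone and fail the resistant one. The Discussion also says that the study will follow the added value of PBO against resistant strains over time. A resistant-strain pass rate that moves with susceptible-strain performance would blur that result. The three PBO nets carry different pyrethroids and PBO doses (Table 3), so nothing ensures that the distortion is equal across products.

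**Working it through.** **Figures in the article.** No stated figure rests on the trigger rule, so there is none to reproduce for it. The mosquito counts next to it do reproduce: 5 pieces × 4 cones × 5 mosquitoes = 100 per strain at baseline, and 4 × 4 × 5 = 80 at follow-up.

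**Routing of a PBO net under the written rule.**

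| Susceptible cone | Resistant cone | Sent to tunnel? | Resistant-strain result available |
|---|---|---|---|
| pass | pass | no | cone pass |
| pass | fail | no | cone failure, no tunnel |
| fail | fail | yes, both strains | cone failure, then tunnel |
| fail | pass | yes, both strains | cone pass already |

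The second row is the problem. The fourth is assumed empty, so that susceptible failures are nested in resistant failures.

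**Formulas.** Let fr and fs be the proportions of nets failing the resistant and the susceptible cone (fs ≤ fr). Let t be the probability of passing the resistant-strain tunnel among resistant-cone failures, taken as the same whether or not the susceptible cone was failed. Count a net with no tunnel result as a failure.

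- Written rule: (1 − fr) + fs × t
- Strain-matched trigger: (1 − fr) + fr × t
- Shortfall: (fr − fs) × t

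The shortfall is zero only if no net fails the resistant cone alone, or if none of those nets would pass the tunnel.

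**Illustration (all rates assumed; the article gives none).** Products X and Y both have fr = 0.70. X has fs = 0.10 and Y has fs = 0.60.

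| t | Matched trigger, both | X as written | Y as written | False gap |
|---|---|---|---|---|
| 0.1 | 0.30 + 0.07 = 37% | 0.30 + 0.01 = 31% | 0.30 + 0.06 = 36% | 5 points |
| 0.2 | 0.30 + 0.14 = 44% | 0.30 + 0.02 = 32% | 0.30 + 0.12 = 42% | 10 points |
| 0.6 | 0.30 + 0.42 = 72% | 0.30 + 0.06 = 36% | 0.30 + 0.36 = 66% | 30 points |

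The gap favours the product that does worse against susceptible mosquitoes.

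**Over time.** Hold fr = 0.70 and t = 0.50. As fs goes through 0, 0.10, 0.30 and 0.60, the written rule gives 30%, 35%, 45% and 60%. A matched trigger gives 65% throughout, and the cone alone 30% throughout. The reported rate would rise only because susceptible-strain performance fell.

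**Ranking.** With t = 0.50, take product A (fr 0.60, fs 0.05) and product B (fr 0.70, fs 0.50). As written: A = 0.40 + 0.025 = 42.5%, B = 0.30 + 0.25 = 55%. Matched: A = 0.40 + 0.30 = 70%, B = 0.30 + 0.35 = 65%. A reversal is therefore possible; nothing in the article shows that it will occur.

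**The case against.** The strongest reply is that the harm requires a combined resistant-strain pass rate, and Table 4 points to the susceptible strain only. On that reading the trigger fits the definition, the resistant-strain result is the cone result, and tunnel findings are shown beside it. Separate reporting by strain would still be met. How untested nets are coded could also be left to an analysis plan. This has some force, but the abstract names both strains for the cone-or-tunnel criteria, and the tunnel section runs resistant mosquitoes. The article never says that the resistant-strain outcome is cone-only. The trigger is also a stated rule, given twice, and not an omitted detail.

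Three stronger readings are tempting and are not supported.

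- *That the main result of the trial is compromised.* The sample size section names attrition as the primary outcome; bio-efficacy is secondary objective iii. The between-product tests in objective v use 24-hour mortality, and the non-inferiority analysis uses the Ifakara Ambient Chamber Test (IACT), which has no cone gate. The IACT is, however, limited to Tanzania at 12 and 24 months.
- *That the error is about 30 points.* That needs t = 0.6, which sits uneasily with nets whose PBO has washed out. If t is small, so is the effect. If nets failing both cones have a lower t than those failing one, the false gap shrinks further.
- *That products are misclassified or misranked.* The rule allows it, but without strain-specific failure rates it cannot be shown.

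**Conclusion.** The point stands as a fault in a stated rule. Followed as written, a cone-or-tunnel pass rate against the resistant strain depends on susceptible-strain cone failure. It falls short of a strain-matched rate by (fr − fs) × t, by an amount that can vary with product and survey.

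The formula rests on nested failures, a common t, and untested nets counted as failures. Dropping untested nets instead would not cure it, because the denominator would then be selected: at t = 0.6, X becomes 0.36 / (0.30 + 0.10) = 90% and Y becomes 0.66 / (0.30 + 0.60) = 73%, against 72% for both with a matched trigger.

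The size is unknown. The scope is one secondary bio-efficacy result for three PBO nets. The susceptible-strain pass rate, MAGNet, attrition and the IACT comparisons are unaffected.

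**What to change.** Define the resistant-strain pass rate on the cone test alone, for every sampled PBO net at every survey. Report resistant-strain tunnel results separately, labelled as coming from the subset that failed the susceptible cone. Reconcile the abstract, Table 4, Mosquito species, WHO cone test procedure and WHO tunnel test so that all give the same definition. This needs no new testing and can be applied to nets already tested, which matters because follow-up is under way. The downside is that a net able to pass only in the tunnel gets no credit against the resistant strain.

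Where tunnel capacity allows, the alternative is a strain-matched trigger: failure of the resistant cone leads to the resistant-strain tunnel, and likewise for the susceptible strain. It costs up to 30 extra tunnel runs (50 at month 36) per PBO product per survey per country. Over follow-up the ceiling is (5 × 30 + 50) × 3 products × 3 countries = 1,800 overnight runs with an animal bait. Introduced part-way, it would also make earlier and later surveys non-comparable unless retained pieces were retested.
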